### Intervention

NMS Assist is a patient engagement system that comprises a front-end patient engagement app and a back-end clinical data management system. Patient engagement systems can communicate with patients to collect data, provide feedback and educational resources, and support the management of a patient-provider relationship. For all Parkinson symptoms, there are pharmacological and nonpharmacological approaches to management. As motor symptoms are already well-supported by digital health solutions, NMS Assist focuses on the nonpharmacological approaches to nonmotor symptoms. It provides initial support for people with Parkinson disease and care partners to identify and manage their NMS before they can be seen by an HCP or need medication. The system’s self-help resources go through the first 3 steps that an HCP would explore with a patient: (1) identifying and describing the symptom using validated questionnaires (Nonmotor Symptoms Questionnaire [NMSQ] [14], Parkinson’s Disease Questionnaire–8 [PDQ-8] [15], and Parkinson’s Disease Questionnaire for Carers [PDQ-C] [16]), (2) explaining why it happens in Parkinson, and (3) providing nonpharmacological approaches to managing it. The system then has the ability to request health care contact for people with Parkinson disease who are still struggling to manage their symptoms so that the HCP can explore further measures. Steps 2 and 3 are supported by self-help videos that use diverse characters and were designed to ensure visual discrimination and easily translatable captions to address visual, hearing, and motor difficulties. The app is also designed to allow care partners to record and monitor their well-being and how they feel the person with Parkinson disease is getting on (see Figure 2). The intervention will be delivered in addition to usual care to the person with Parkinson disease.

**Figure 2 figure2:**
[figure not shown]
NMS Assist system features. PwP: People with Parkinson disease. NMS: Nonmotor symptoms. HCP: health care professionals.

### Sample Selection and Recruitment

People with Parkinson disease attending outpatient clinics through the University Hospitals Plymouth NHS Trust Parkinson service are eligible for this study (see Textbox 1 for eligibility criteria). All people with Parkinson disease and care partners who are willing and eligible will be included, with the intention of recruiting a representative sample based on various demographic and Parkinson-specific characteristics. The participants invited to the semistructured interview will be randomly selected from within different demographic and disease characteristic categories; we will continue recruitment in the semistructured interviews until we have reached demographic saturation to ensure we complete in-depth qualitative understanding of the impact of the system.

Recruitment will take place through the Plymouth Parkinson service. People with Parkinson disease attending outpatient clinics at the Plymouth Parkinson service will be invited to participate in the study along with their care partner. The associated HCPs responsible for the care of people with Parkinson disease and care partner dyads who consent into the study will then be invited to participate as well. Patients will be recruited during clinical appointments with the Plymouth Parkinson service by research nurses who will provide them with a paper participant information sheet to consider and will collect verbal or written consent using a preestablished informed consent form. Associated HCPs of the people with Parkinson disease who consent into the study will be invited to participate in the study for use of the clinician portal (and provided with an HCP version of the participant information sheet and informed consent form).

Selection criteria. NMS: Nonmotor symptoms.Inclusion criteria:Willing and able to provide informed consent and comply with intervention requirementAged 18 years or olderBe fluent in EnglishNot resident in a care or nursing homeAmbulatoryHave compatible smartphone and data accessNormally under the care of the Parkinson service in the participating organizationParticipant’s health care professional in the participating organization consented to participate in the studyExclusion criteria:Incapable of self-consentSecondary cause of parkinsonismSignificant cognitive impairment or a diagnosis of Parkinson disease dementiaLiving in residential care facilitiesPrevious involvement in development or testing of the NMS Assist systemA life expectancy of <6 monthsSignificant comorbidity, which in the opinion of the chief investigator would preclude safe participation in the study or protocol complianceIn a dependent or unequal relationship with the research or care teams or any patient and public involvement representatives

### Sample Size

We will recruit 60 people with Parkinson disease–care partner dyads and their associated HCPs—the exact number of HCPs cannot be determined until the people with Parkinson disease–care partner dyads have been recruited, as we will include HCPs who are associated with those patients. Of the 60 dyads, at least 20 people with Parkinson disease–care partner dyads will be purposively sampled for a semistructured interview. We will also be inviting the HCPs associated with those dyads to separate semistructured interviews.

Since this is a feasibility study, a formal sample size calculation has not been performed. A sample size of 60 people with Parkinson disease–care partner dyads was selected because this is an achievable number of patients to recruit within the study period based on our prior research.

### Outcomes

#### Primary Outcome

The primary outcome, patient activation, will be assessed using the Patient Activation Measure [17]. The concept of patient activation refers to patients having the necessary knowledge, confidence, and skills to manage their own health and well-being. It is important to note that as this study design is centered on feasibility, the evidence captured will not measure efficacy. Should there be indications of a positive impact of the NMS Assist system on patient activation and health and well-being outcomes, efficacy will be tested in further studies.

#### Secondary Outcomes

There will be several secondary outcome measures to assess health and well-being outcomes, safety, feasibility, usability, and acceptability (see Textbox 2).

Secondary outcomes and measures. EQ-5D-5L: EuroQol 5 Dimension 5 Level. NMS: Nonmotor symptoms.1. Health outcomesNonmotor Symptoms Questionnaire [14]Movement Disorder Society–Nonmotor Rating Scale [18]Parkinson’s Disease Questionnaire–8 [15]Parkinson’s Disease Questionnaire–39 [19]EQ-5D-5L [20]2. Well-being outcomesWarwick-Edinburgh Mental Wellbeing Scale [21]Parkinson Disease Questionnaire for Carers [16]3. SafetyAggregated evaluation resultsAdverse event reporting4. Healthcare contactsNumber of patient-initiated contacts with health care team (through the ‘request health care contact’ feature)Number of health care professional–initiated contacts (NMS Assist system has identified a need for clinical intervention based on patient- or care partner–reported data and prompted the health care professional to contact patient) recorded by the system5. FeasibilityTechnical issues identified from the system use dataTechnical issues identified by participants6. UsabilitySystem Usability Scale [22,23]Qualitative feedback from semistructured interviews7. AcceptabilityQualitative feedback from semistructured interviews (structured using the theoretical framework of acceptability) [11]8. EngagementSystem use data (trend of use over time)Qualitative feedback from semistructured interviews9. CostsCost analysis will be used to examine the factors impacting costs for implementing the system

##### Health and Well-being Outcomes

A key element of the NMS Assist system is the use of validated questionnaires, and several of the health and well-being outcomes will be measured through the app—including the NMSQ [14], the short form of the PDQ-8 [15], and the PDQ-C [16]. The questionnaires have been validated in several different populations (eg, NMSQ [14,24-26], PDQ-8 [27-31]), suggesting that the measurement properties are appropriate for people with Parkinson disease in different contexts [32].

During the clinic visits (at baseline, 6 months, and 12 months), health and well-being outcomes will be assessed using the long-form PDQ-39 [19], the Warwick-Edinburgh Mental Wellbeing Scale (WEMWBS) [21], the Movement Disorder Society–Nonmotor Rating Scale (MDS-NMS) [18], and the EQ-5D-5L (EuroQol 5 Dimension 5 Level) [20]. These validated measures will be used to gather more in-depth data about people with Parkinson disease symptoms and their impact on people with Parkinson disease and care partner well-being to provide additional evidence of the impact of the system on health and well-being. This will also enable an assessment of the validity of home-collected measures.

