### Rationale

#### Benefits for People With Parkinson Disease and Care Partners

NMS Assist is expected to have several benefits for people with Parkinson disease and care partners; notably, by improving symptom monitoring by making assessments more timely, relevant, and convenient, by increasing disease and symptom awareness, and by supporting people with Parkinson disease and care partners in managing their NMS at home. A formative usability evaluation of 13 users (9 people with Parkinson disease, 4 care partners) demonstrated satisfaction with the system (System Usability Score 80%) [8].

The usability study identified 11 critical issues for improvement, centered on 3 themes: navigation, content, and accessibility [8]. These aspects of the system were subsequently refined based on participants’ suggestions. To reduce the length of the NMSQ, people with Parkinson disease can complete partial assessments to monitor their symptoms. However, they are asked to complete the length of the Nonmotor Symptoms Questionnaire (NMSQ) every 6 months to ensure that a holistic assessment is performed, providing clinical safety netting.

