#### Quantitative Data Collection

The primary outcome, patient and care partner activation, will be completed at the beginning of the intervention period and monthly thereafter to measure the impact of NMS Assist on the knowledge, confidence, and skills of people with Parkinson disease and care partners over time [17] (see Figure 1). People with Parkinson disease and care partner scores on the NMSQ, PDQ-8, and PDQ-C will be recorded automatically by the system. The proportion of people with Parkinson disease who are contacted by their nurse or clinician based on their symptom questionnaire responses will be measured. Quantitative app and portal use data will be captured by the system to examine patterns of engagement with the questionnaires, self-help resources, and triggered health care contacts. Data about participant characteristics, recruitment, and retention will also be recorded.

Participants will also be asked to attend 3 study visits, at baseline, 6 months, and 12 months (see Figure 1), where they will complete the long-form PDQ-39 [19] and the Warwick-Edinburgh Mental Wellbeing Scale (WEMWBS) [21] and will have administered the Movement Disorder Society–Nonmotor Rating Scale (MDS-NMS) [18] and the EQ-5D-5L [20].

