### Data Analysis

The primary analysis will be the comparison of mean Patient Activation Measure scores [17] at each month. A repeated measures analysis of variance will be conducted to identify any significant changes in mean Patient Activation Measure scores over the 13 time points (baseline and monthly until 12-months postbaseline). If the normality assumption for a repeated measures analysis of variance is not met, a nonparametric alternative will be used.

The same analysis for the primary outcome will be conducted for the health and well-being outcome measures and the System Usability Scale, comparing the measure scores at the baseline, midpoint, and end points. Exploratory analyses will be conducted to identify potential associations between demographic or disease characteristics and outcome measures to inform hypotheses for future evaluations. All other quantitative data will be analyzed using descriptive statistics.

Semistructured interviews will be coded by 2 investigators using thematic analysis [40]. Triangulation of the quantitative questionnaire, system use, and qualitative semistructured interview data will be conducted to validate findings.

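### The PDQ-C, the only carer-specific quality-of-life measure, is described as collected through the app and not at study visits, so care partners who stop using NMS Assist would have no later score.

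*Protocol article*

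**What the plan says.** The article splits seven health and well-being instruments between two routes.

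- **App.** Under Health and Well-being Outcomes, "several of the health and well-being outcomes will be measured through the app"; the three named are the NMSQ, PDQ-8 and PDQ-C. Quantitative Data Collection repeats this: "People with Parkinson disease and care partner scores on the NMSQ, PDQ-8, and PDQ-C will be recorded automatically by the system".
- **Visits.** "During the clinic visits (at baseline, 6 months, and 12 months), health and well-being outcomes will be assessed using the long-form PDQ-39", together with the WEMWBS, MDS-NMS and EQ-5D-5L. Quantitative Data Collection lists the same four. The PDQ-C is in neither visit list.

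Data Analysis applies the primary outcome's repeated measures analysis of variance to the health and well-being measures, "comparing the measure scores at the baseline, midpoint, and end points".

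The Rationale says of the NMSQ: "To reduce the length of the NMSQ, people with Parkinson disease can complete partial assessments to monitor their symptoms". It then asks for the complete questionnaire every 6 months.

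**The concern.** For these three questionnaires the intervention is also the data collection tool, so whether a later score exists depends on whether the person still uses the intervention. The article expects some people to stop: Table 1 plans to record retention and to explore reasons for discontinued use, and Study Duration and Follow-up offers no incentives for adherence.

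The PDQ-C is the most exposed. Care partner quality of life is part of the research question, of the first objective and of the value proposition domain in Table 1, and the PDQ-C is the only carer-specific instrument in the list of secondary outcomes. A care partner who gave up the app for lack of benefit could attend the 12-month visit and still contribute no end score. How to analyse missing values can be left to a statistical analysis plan, but no analysis can recover a score that was never requested.

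**Working it through.** **1. Which instruments have a second route**

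| App instrument | Nearest instrument listed at visits |
|---|---|
| PDQ-8 (patient quality of life) | PDQ-39, the long form |
| NMSQ (nonmotor symptoms) | MDS-NMS |
| PDQ-C (care partner quality of life) | None that is carer-specific; the WEMWBS measures general well-being |

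If a patient stops using the app, symptom and quality-of-life data still arrive through the visits. For the care partner, the carer-specific measure does not.

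**2. Which time points are affected**

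Baseline is taken at the start, before anyone can disengage. A care partner who stops before month 6 loses the midpoint and end scores; one who stops between months 6 and 12 loses the end score. A repeated measures analysis of variance in its usual complete-case form drops both.

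**3. Size of a possible bias**

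The article states no stopping rate, effect size or SD, and Sample Size says that no formal calculation was made, so there is no planned figure to reproduce. The only input from the document is the 60 dyads. The rest are assumptions:

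- r = share of care partners still completing the PDQ-C in the app;
- D = mean change in continuers minus mean change in stoppers, in SD units.

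The mean in all enrolled is r × (continuers' mean) + (1 − r) × (stoppers' mean). The observed mean is the continuers' mean. Subtracting gives:

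bias = (1 − r) × D, and standard error of the observed mean change = 1/√(60r).

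| r | Observed of 60 | Missing | Bias, D = 0 | D = 0.2 | D = 0.5 | D = 0.8 | Standard error |
|---|---|---|---|---|---|---|---|
| 0.9 | 54 | 6 | 0 | 0.02 | 0.05 | 0.08 | 0.14 |
| 0.8 | 48 | 12 | 0 | 0.04 | 0.10 | 0.16 | 0.14 |
| 0.7 | 42 | 18 | 0 | 0.06 | 0.15 | 0.24 | 0.15 |
| 0.5 | 30 | 30 | 0 | 0.10 | 0.25 | 0.40 | 0.18 |

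At D = 0.5, 20% stopping gives 0.20 × 0.5 = 0.10 SD, below one standard error (0.14). With 50% stopping it is 0.50 × 0.5 = 0.25 SD, above one standard error (0.18). The bias is zero if stoppers change as continuers do, but the 12 to 30 scores are lost either way. The part that visit collection can recover is the part from people who still attend.

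**The case against.** **Collection only in the app is an inference.** No sentence says so. The Sensitivity section says that outcome measures reach patients by app or through their health care professional, without assigning instruments, and Figure 1, which the article cites for data collection points, is not shown. This lowers confidence but does not remove the point. Two sections give the same four visit instruments and put the PDQ-C with the app. Where a route outside the app is intended, the article names it: the usability questions go out as online or paper surveys at visits.

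**Visits may cover care partners.** The visit measures are said to address symptoms and "their impact on people with Parkinson disease and care partner well-being to provide additional evidence of the impact of the system", and the WEMWBS is listed beside the PDQ-C as a well-being outcome. So it would go too far to say that care partners yield no outcome data after stopping. But the article does not plainly say that care partners complete the WEMWBS, and it is not a carer quality-of-life scale.

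**Partial NMSQ totals.** A reader might infer that partial and full totals would be mixed in the comparison. The article does not support that: a complete NMSQ is requested every 6 months, which matches the comparison points.

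**Home-versus-clinic check.** On the visit measures the article says, "This will also enable an assessment of the validity of home-collected measures". A reader might infer that home and visit scores would be unmatched in time. With Figure 1 not shown this cannot be established, and a pairing window is detail that an article may leave out.

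**Low stakes.** These are secondary outcomes in a single-arm feasibility study that disclaims efficacy and lists its ability to assess health and well-being outcomes as a limitation. Questionnaire completion is itself reported, so selective completion would be visible. All of this stands and limits the weight of the point. But seeing the selection does not recover the missing scores.

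**Conclusion.** The point holds for the PDQ-C. As described, care partners who stop using NMS Assist but still attend visits have no route to a later PDQ-C, and the change over time may reflect continuing users only. The NMSQ and PDQ-8 share the gap to a lesser degree, because related measures are taken at visits.

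A reader might go further and conclude that the care partner result is biased, or that baseline scores are affected too. Neither follows. Bias needs both a material stopping rate and a difference between stoppers and continuers, and the article gives neither; baseline comes before disengagement. With 20% to 50% stopping and an assumed difference of 0.5 SD, the bias would be 0.10 to 0.25 SD. With 10% stopping it would be 0.05 SD, and with no difference zero. The conclusion also assumes that the full protocol and Figure 1 add no visit collection of the PDQ-C.

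**What to change.** At the baseline, 6- and 12-month visits, have every care partner complete the PDQ-C on paper, whether or not they still use NMS Assist. Ideally, have every patient complete a full NMSQ in the same way. State in Data Analysis that these visit scores are the ones compared at baseline, midpoint and end. Using paper at all three visits also keeps the mode of completion constant.

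Keep app-entered scores for engagement and monitoring. The visit copies should stay outside the app. Entering them in the app at clinic would raise the questionnaire completion and system-use measures in Table 1, and could prompt contacts that are themselves counted as an outcome. The PDQ-8 can remain as it is.

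The cost is a few extra minutes at visits that already take place, some duplication for active users, and a sentence each in Quantitative Data Collection and Data Analysis. Care partners who stop attending visits as well would still be missing.

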##### Safety

We do not anticipate any significant safety risks from the intervention as the self-help guidance was collected from credible resources, but safety will be assessed by maintaining an adverse event report log.

##### Health Care Contacts

The use of the health care contact function will be assessed by examining the number and frequency of people with Parkinson disease– and HCP-initiated contacts through the system.

##### Feasibility

Feasibility will be assessed by examining any technical issues identified in the system and system use data (including logs of complaints made by participants during the intervention delivery period) as well as asking participants about any technical issues they encountered when using NMS Assist during the semistructured interviews.

##### Usability

Usability will be assessed using questions presented to people with Parkinson disease, care partners, and HCPs delivered by online or paper surveys distributed to participants during their clinical visits at the beginning, midpoint, and end of the study delivery period. These questions will be drawn from the System Usability Scale [22]. Usability will also be assessed during the qualitative semistructured interviews by asking about any usability issues or barriers (not due to technical malfunctions) encountered by the users.

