### Dissemination Plan

Analysis of the data will be compiled into a published peer-reviewed paper. People with Parkinson disease, care partners, and HCP investigators involved in the project will be integral in disseminating the results. PPI representatives will help develop and edit communications for all audiences, but, in particular, the summary of results that will be sent to all study participants. They will take the lead in disseminating and presenting results to the broader Parkinson community and professional groups such as through patient networks, the Parkinson’s UK research network, patient and care partner congresses and conferences and the World Parkinson’s Congress (which includes patients and professionals), newsletters, articles, and social media. Academic members of the project team will disseminate the results through peer-reviewed journal publications and at research conferences.

The newest version of NMS Assist will be made publicly available to people with Parkinson disease and care partners after the system refinement stage (6 months after project commencement). This access will be available concurrent to our study, and members of the public will have the ability to consent into the study if they choose. We will make the data collected by NMS Assist freely accessible for research purposes by creating a data set that can be stored and shared securely in a data safe haven. To ensure that this data asset is used most appropriately, we will consult with Parkinson’s UK and other stakeholders when developing our data sharing policy. In future, this will enable us to provide free and secure access to the data for people who apply to use it for research purposes, while accounting for data security and ethical considerations.

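### The first System Usability Scale score most likely precedes use of NMS Assist, so the three-point SUS ANOVA can register expectation rather than a change in usability

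*Protocol article*

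**What the plan says.** The protocol article's Usability section gives SUS questions to patients, care partners and health care professionals (HCPs) by online or paper survey, "distributed to participants during their clinical visits at the beginning, midpoint, and end of the study delivery period". Quantitative Data Collection fixes the visits: "Participants will also be asked to attend 3 study visits, at baseline, 6 months, and 12 months".

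Data Analysis names the method for the primary outcome: "A repeated measures analysis of variance will be conducted to identify any significant changes in mean Patient Activation Measure scores", with a nonparametric alternative if normality fails. It applies the same analysis to the "health and well-being outcome measures and the System Usability Scale, comparing the measure scores at the baseline, midpoint, and end points".

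The selection criteria exclude anyone earlier involved in developing or testing the system. The article describes no onboarding or trial-use period before the first SUS. Usability is also explored in interviews. According to the abstract's conclusions, supportive evidence on usability is one of the study's success criteria.

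**The concern.** A usability score means something once the respondent has used the system. At the first visit a clinic-recruited patient or care partner will generally not have done so. Their answer records what they expect or how the app first strikes them, while the two later answers record experience. An ANOVA across all three treats two constructs as repeated measurements of one.

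The result can mislead in either direction. A highly usable app that meets very high expectations can show a significant fall. A poor app that meets equally low expectations can show no difference. Usability evidence feeds the success criteria and the judgement on wider adoption. For that decision, what matters is how usable people find the system after using it.

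**Working it through.** **No figure to reproduce.** The article gives no SUS standard deviation, target, alpha or power, and says that no formal sample size calculation was done. The check is a reading of the sections together, followed by an illustration on assumed values.

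**Reading.**
1. Usability: the first SUS falls at the start of the delivery period.
2. Study Duration and Follow-up: delivery is the 12-month intervention phase, so its start is the start of access for a clinic recruit.
3. Selection criteria: people who had already tested the system are excluded.
4. Data Analysis: baseline is one of three compared levels for the SUS.

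Together these make a pre-use first score the most plausible reading for patients and care partners, and that score enters the test.

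**Illustration.** Inputs: n = 60 (Sample Size). Assumed: two-sided alpha 0.05; SUS SD 12.5 or 20; correlation 0.2 between baseline and each later score and 0.6 between the two later scores; true mean identical at 6 and 12 months; baseline mean shifted by d points. Method: repeated measures ANOVA with Greenhouse-Geisser correction, 3,000 simulated studies per row.

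| SD | d | Three-point test rejects | 6 vs 12 months only rejects |
|---|---|---|---|
| 12.5 | 0 | 0.051 | 0.048 |
| 12.5 | 3 | 0.323 | 0.051 |
| 12.5 | 5 | 0.707 | 0.049 |
| 12.5 | 8 | 0.977 | 0.052 |
| 12.5 | 10 | 0.999 | 0.045 |
| 20 | 0 | 0.044 | 0.054 |
| 20 | 3 | 0.151 | 0.045 |
| 20 | 5 | 0.343 | 0.053 |
| 20 | 8 | 0.704 | 0.050 |
| 20 | 10 | 0.877 | 0.047 |

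The simulation lowered the baseline mean. By symmetry, raising it gives the same rates.

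**Check by hand.** The contrast of baseline with the average of the two later scores has variance SD² × [1 + (1 + 0.6)/2 − 2 × 0.2] = 1.4 SD². Its standard error is SD × √(1.4/60) = 0.153 SD, which is 1.91 points at SD 12.5 and 3.06 at SD 20. A 5-point gap is then 5/1.91 = 2.62 or 5/3.06 = 1.64 standard errors. By the normal approximation, rejection is Φ(2.62 − 1.96) ≈ 0.74 or Φ(1.64 − 1.96) ≈ 0.37. The omnibus test spreads the same signal over two degrees of freedom and comes out slightly lower, at 0.707 and 0.343, as expected.

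**What the post-use scores can say.** The 95% half-width of one post-use mean is 1.96 × SD/√60. That is 3.2 points at SD 12.5, 3.8 at SD 15 and 5.1 at SD 20. With 48 respondents (an assumed 20% loss) it is 3.5, 4.2 and 5.7. This is the precision of data already planned. It is not the size of the defect.

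**The case against.** The strongest reply is that the article never says the first SUS comes before first use. The study diagram is not shown. The survey may be online and is only handed out at the visit, so it could be completed later. Several questionnaires run in the app, so onboarding around the first visit is possible. The Dissemination Plan adds a route for existing users: "This access will be available concurrent to our study, and members of the public will have the ability to consent into the study". The tester exclusion sits in a list that reads as patient criteria, and an HCP with several dyads may know the portal before the later ones start. All of this stands. Pre-use timing is an inference. It is a strong one for clinic-recruited patients and care partners and is not established for HCPs or public joiners.

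It also stands that the ANOVA is an omnibus test. Baseline is one of three levels, not a named comparator, and the midpoint-to-end contrast lies wholly after use.

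A reader might infer that the whole SUS analysis fails, or that usability after use is never obtained. The documents support neither. The 6- and 12-month scores are collected, comparing means yields them, interviews add to them, and the success criterion sets no test or threshold. Nor does the article say that the three user groups are pooled; that is detail commonly left to the full protocol or SAP. The formative score of 80% is not stated as a benchmark. It came from 9 patients and 4 care partners, on a version that was later refined.

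The reply does not reach the core. Both the time point and the test are written down, and together they put a probable expectation score into a test of change in usability.

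**Conclusion.** The point holds in a confined form. As written, the SUS test includes a first score that most likely reflects expectation, so its result, significant or null, cannot be read as showing whether usability changed. Under the assumed SDs and correlations, with constant usability and a 5-point gap at baseline, the test is significant in 34% to 71% of studies; with a 10-point gap, in 88% to 99.9%. The real gap is unknown and could be zero, in which case the rate stays near 5%.

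The defect is limited to the baseline score and to comparisons that include it, for one secondary outcome of a feasibility study that disclaims efficacy. It is worth correcting because the SUS contributes to a success criterion and the correction is nearly free. If the full protocol schedules use of the app before the first SUS, the concern falls away and the article need only say so.

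**What to change.** Choose one of two routes and state it in the protocol and SAP:

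- Give the first SUS after a defined period of use, for example through the online survey already planned, and state that period.
- Or keep the baseline administration, label it expected usability, report it descriptively and exclude it from the SUS ANOVA.

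Under either route, base the usability conclusion on the post-use SUS mean with its 95% CI at 6 and 12 months, and test change only between post-use time points. The formative score of 80% can be cited as context for patients and care partners. It should not serve as a benchmark for HCPs, none of whom contributed to it.

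The cost is a change of wording plus either a shifted survey date, which gives up the pre-use score, or one time point fewer in the test. The 6- and 12-month data collection is unchanged.
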